#### Training of staff to deliver brief advice

Participating primary care staff will receive a one hour training session on how to deliver five minutes of brief advice according to the protocol. The aim of the training will be to provide practitioners with the skills necessary to effectively and empathically deliver brief advice about alcohol risk to patients in their practice. The training was developed by the SIPS team to be delivered by an Alcohol Health Worker (AHW). The AHWs in the SIPS team are experienced practitioners in the field of alcohol treatment. They contributed to the development of the training package and have been fully trained to deliver the training to practitioners. The training package is based on a PowerPoint presentation with scripts to standardise delivery. The training sessions are adapted for use in the different experimental conditions in which BA is being delivered.

The session will be presented to small groups of clinicians who will be encouraged to interact with the trainer, ask questions and comment on the content. This will be followed by interactive role play in which the AHW demonstrates the intervention and each practitioner then has an opportunity to practice with a co-worker, observed by the trainer who provides feedback and encouragement. We envisage that training sessions will be delivered to groups of 1–10 practitioners with 3–4 being the typical group size.

#### Training of staff to deliver brief lifestyle counselling

Primary care staff who are suitable to deliver brief lifestyle counselling will receive formal training and supervision on Brief Lifestyle Counselling, in addition to the Brief Advice training. The training will be based upon the previous work of Rollnick et al. [32] in addition to experiences from an earlier trial of screening and brief interventions [33]. The training will comprise four main elements: orientation to the relevant practice, standardised PowerPoint presentation, tape recorded simulated consultations with trained actors and ongoing clinical supervision provided by experienced AHWs.

The simulated consultations will be recorded and rated by three independent clinical assessors. The practitioner will be assessed for adherence to the BLC protocol in addition to their behaviour and skills using the Behaviour Change Counselling Index (BECCI) [34]. Assessors will submit BECCI ratings, comments and supervision points for each consultation. This information will support clinical supervision and training until the practitioner reaches a required standard of practice agreed by an independent clinical assessor.

Support regarding the paperwork for the research will be provided by a research team member, who will also act as the site study coordinator. Research staff and trainers will maintain regular contact with practices throughout the study period, including site visits and telephone support.

### Outcome Measures

#### Staff attitudinal and organisational measures

Participating staff in practices will be surveyed before and after training in each condition of the study to assess attitudinal factors and factors influencing implementation of screening and brief intervention procedures.

Attitudes will be assessed via the shortened Alcohol and Alcohol Problems Perception Questionnaire (SAAPPQ) [35]. A list of all professional staff that can deliver alcohol screening and brief intervention in each study site will be compiled. A self-administered SAAPPQ will be distributed to participating staff on three occasions: pre-training, post-training and post-study. SAAPPQ has five subscales covering role adequacy, role legitimacy, self-esteem, motivation, and work satisfaction. Role adequacy and role legitimacy are concerned with role security, i.e., how individuals perceive the adequacy of their skills and knowledge in relation to problem drinkers and how appropriate it is for them to work with such clients. The subscales relating to self esteem, motivation and work satisfaction, are concerned with worker's therapeutic commitment, i.e., the extent to which they seek to engage drinkers in treatment and the extent that they find the work rewarding on both a professional or personal level [36].

In addition to the SAAPPQ, the post-training and post-study questionnaires will contain a number of semi-structured and open questions developed to elicit information on staff attitudes towards alcohol screening and brief intervention; previous experience of delivering alcohol screening and brief intervention; readiness to undertake these activities; the training needed to conduct screening and brief intervention; the suitability of each site to provide SBI; and potential barriers to effective implementation.

Factors relevant to implementation of screening and brief intervention have been found to be divided into *predisposing*, *enabling *and *reinforcing *factors [37]. Predisposing factors relate to clinicians' willingness to implement screening and brief intervention. Enabling factors are the skills and resources needed to implement screening and brief intervention. Reinforcing factors are visible results, feedback from peers and patients and other factors that encourage continuation of screening and brief intervention.

In the USA, Babor et al. [37] collected data on these factors in two ways: (1) surveys of providers and specialists completed prior to training, after training and at the end of project operations (five items) and (2) independent ratings of site factors made by two research staff during regular technical assistance contacts and site visits (17 items). Inter-rater reliability in Babor et al. [37] was high for all factors (median *r *= 0.70).

In the USA study, predisposing factors were: (1) peer approval for alcohol screening; (2) organizational approval for alcohol screening; (3) the frequency clinicians asked about alcohol consumption; (4) the frequency clinicians educated patients about health risks; (5) the frequency clinicians advised patients with problem drinking to cut down or stop drinking; (6) stable patient membership was based on researcher ratings of whether patient membership was stable or changing; and (7) organisational instability based on ratings of fiscal and management stability. Enabling factors were derived from ratings conducted by two research staff. These factors were: (8) number of clinicians trained at each clinic; (9) doctors' time; (10) nurses' time, (11) receptionists' time; (12) doctors' turnover; (13) nurses' turnover; (14) receptionists' turnover; (15) competing organizational priorities; (16) having an influential site coordinator; (17) involvement of clinic staff in planning; (18) facilitation by computer technology; (19) amount of technical assistance; and (20) successful procedural changes. Two factors classified as reinforcing implementation were also derived from the research staff ratings: (21) organisational support; and (22) financial incentives. An average organizational score was created based on the sum of the 17 items the two researchers rated. This score indicated the total extent of favourable predisposing, enabling and reinforcing factors observed at a given clinic.

In this study we will survey primary care staff before and after training and compare the above factors between different implementation models.

#### System measures

The research team will identify the total number of patients aged over 18 years who attended the practices during the recruitment period, the total number of patients screened, the number screening positive and the number receiving an alcohol intervention in each of the 3 implementation models. This will allow calculation of the overall screening rate, the screen conversion rate (proportion of positive screens) and the intervention rate in the different settings. We will also compare these measures between practices assigned to universal versus targeted screening and the FAST versus M-SASQ screening tools.

Patient re-attendances at practices over the 6 and 12 month follow-up periods will be assessed using computerised records and compared with attendances by participating patients in the 12 months before entry into the study. The sustainability of the screening and intervention approaches will be assessed by examining the extent to which screening and intervention activity continues after the end of the formal study recruitment period.

#### Patient measures

A summary of the measures used with patients and the stage that they are administered are summarised in Figure 1.

**Figure 1 F1:**
[figure not shown]
**Measures used with patients and the stage that they are administered**.

##### Baseline

Immediately before receiving the initial PIL and/or brief advice intervention, participants will be invited by the primary care staff to provide contact details and complete the Extended AUDIT[29], Euroqol (EQ-5D) [38], a short service use questionnaire (S-SUQ) [39] and modified Readiness Ruler [40]. Participants in the extended intervention will complete the baseline at the same stage as those in other groups.

AUDIT is normally used as a screening test for alcohol use disorders [29]. However in this context the AUDIT will be used as a means of establishing the severity of alcohol use disorders at baseline, in a way that is least intrusive to naturalistic aim of the trial in the primary care setting and as a means of measuring the adequacy of matching between the intervention groups at baseline. The AUDIT contains 10 items to measure alcohol consumption, alcohol problems and dependence over, in this case, the previous 6 months, and the sum of the item scores provides a measure of severity which has been used in several previous studies, allowing comparability with other primary care samples [1]. We felt that the use of more elaborate baseline alcohol consumption measures would interfere with the naturalistic aims of the study and possibly would contribute a form of intervention in itself, so introducing bias into the evaluation of the interventions by reducing the difference between trial interventions. In addition, participants will complete the EQ-5D as a brief 5-item measure of quality of life [38]. Use of health, social criminal justice services and wider societal costs will be measured via a shortened version of Service Use Questionnaire [39] which allows estimation of health care and wider social costs for health economic analysis in the six months prior to intervention. A modified Readiness Ruler [40] containing a zero to ten scale of the extent to which participants think about their drinking as a problem or have addressed this issue will assess participants' motivational state regarding changing their drinking behaviour.

##### Follow-up

At 6 and 12 months after intervention, all patients will be contacted via telephone or post as preferred by research staff who will be blind to their intervention condition. Patients will be offered telephone, postal or face-to-face follow-up as preferred. Researchers will administer the shorter Alcohol Use Disorders Identification Test (Extended-AUDIT) [41]. Alcohol-related problems will be assessed via the brief Alcohol Problems Questionnaire (APQ) [42]. We will also re-administer an extended version of the Service Use Questionnaire SUQ [39], EQ-5D [38]. Patient satisfaction with the advice/help received during the intervention will be assessed using a modified version of the Patient Satisfaction Questionnaire (short form) at 12 months [43].

At follow-up, each patient will also be asked if, and how often, they made use of the Drink-Line telephone number.

All intervention tools and protocols are available from the SIPS study website .

### Financial incentives

Research causes significant disruption to busy practices as well as occupying additional clinical time (consent, assessment, training, data collection procedures etc.). Clinicians are unlikely to participate in a research trial without incentivisation [44] and retention of practices in the trial may also be at risk [45]. However, in this pragmatic trial we were cognisant of the need to evaluate interventions in such a way as to reflect routine primary care. Paying clinicians pro rata for clinical behaviour could undermine our ability to assess implementation outcomes on the basis of acceptability of screening and brief intervention models or how well these have embedded in practice systems. Thus we separated incentives into payment for research participation and for clinical activity.

We will incentivise research participation via the payment of £3,000 to each practice, subject to successful patient recruitment. Payments will be staged, with £1,000 paid at the outset after taking part in the training, £1,000 paid on completion of successful recruitment of participants and £1,000 paid at end of data collection. We hope this schedule of payments will ensure that practices will remain in the trial throughout the study period. A minimum threshold is set of recruiting 31 cases per practice, which would entail screening at least 155 patients per practice since 20% of patients in primary care are likely to be hazardous or harmful drinkers [6]. This will cover the time and disruption caused by participating in the research study. However, practices may stop at this minimum case number.

We will also incentivise screening and brief intervention clinical activity as if this was part of the Quality and Outcomes Framework (QOF) in core general medical services (GMS). We will model the payment on smoking cessation work in the Quality Outcomes Framework (QoF) where points are awarded for building a register of cases and for delivering advice (in 2005, 1 point = £125). At this time, in the coronary heart disease area of QOF, GPs gained 6 points for building a case register (£750) and 10 points for a specific percentage of cases receiving advice (£1,250). We will use practice-level figures (from PCT commissioning colleagues) to scale payments to a per patient fee accordingly (See Table 2).

**Table 2 T2:** Incentives for screening and brief intervention activity

Average practice list size	5,500
Number of eligible adults in the practice	2,250

We assumed 1/3 adults screened	750 cases

Screening fee = 750/750	£1 per patient screened

We assuming 1/5 cases were screen positive	150 cases

Advice fee = 1,250/150	£8 per patient advised*

Counselling is four times longer than advice	31 cases required

Counselling fee	£32 per patient counselled.

* This fee will also be given to control practices delivering the leaflet.

### Participant incentives

Each patient participant will receive a £10 voucher, together with a Thank You letter in the post shortly after completing the baseline research questionnaires and another £10 voucher for completing the 6 and 12 month research follow-up interview.

### Economic evaluation

The economic component of the study will consist of a cost-effectiveness and cost-utility analysis. The study aims to identify, quantify and value resources related to alcohol SBI by clinicians in primary care and the subsequent use of health, social care and criminal justice services by patients following each type of intervention.

Resources utilised in the identification and brief intervention delivery or control condition will be recorded by practice staff involved on an ongoing basis. This will allow the calculation of costs of implementation of different models of screening and brief intervention. Local values will be used to calculate the costs of the interventions, which will include staff costs, premises costs and costs of leaflets and other consumables. In addition, specific training costs for staff will be calculated, in terms of staff time, premises costs and the cost of training materials.

Patients' use of health, social care and criminal justice services will be identified retrospectively using a short SUQ and applying a common set of national unit cost estimates. Patient costs in the 6 month period before SBI can then be compared to cost in the 6 month period after SBI to explore any changes in costs imposed by patients in each group.

The economic analysis will calculate the incremental cost-effectiveness of the control condition with each of the screening and brief intervention conditions under study, using measures of clinical outcome and quality of life responses at 6 and 12 month follow-ups. The use of EQ-5D enables the estimation of Quality Adjusted Life Years (QALYs). Data will be bootstrapped to account for the expected skewness evident in economic cost data [46]. The analysis will include the construction of cost-effectiveness acceptability curves to illustrate the probability that the brief intervention is more cost-effective than usual care, based on different monetary values being attached to QALYs. The use of QALYs follows the recommendations of NICE [47] and enables the value for money afforded by treatment to be compared to a range of other health care interventions. Furthermore, combination of the economic cost data and outcome data with patient data collected in the trial will enable a secondary analysis of various patient characteristics that may influence the cost-effectiveness of the intervention.

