### Design

The trial has a 2 × 2 × 3 nested factorial design encompassing screening approach (targeted versus universal screening), screening method (the Fast Alcohol Screening Test (FAST) [25] or a modified Single Alcohol Screening Questionnaire (M-SASQ)) [26]) and brief intervention intensity (Patient information leaflet (PIL); Brief advice (BA); Brief lifestyle counselling (BLC)). The main advantages of utilising a factorial approach are twofold. First each of the three elements (screening approach, screening tool and intervention) can be analysed independently with sufficient power to make meaningful interpretation of relative effectiveness. Second, the method enables meaningful interpretations of the relative effectiveness of any combination of screening approach, screening tool and intervention modality.

We will recruit 24 general practices from the North East, London and the South East of England. Practices will be randomly assigned to 1 of 2 screening approaches (12 practices in each approach), 1 of 2 screening tools (12 practices using each tool) and 1 of 3 intervention conditions (8 practices in each condition) as shown in Table 1. Since we expect that there may be a difference in uptake of screening between intervention conditions, we expect the recruitment to take varying periods of time in the different conditions.

**Table 1 T1:** SIPS Primary Care trial design

**Intervention condition**		North			London & the South East			
**Screening condition**		Leaflet	Brief Advice	Brief Counselling	Leaflet	Brief Advice	Brief Counselling	Totals

Targeted presentation	FAST	31	31	31	31	31	31	186 (6)
	M-SASQ	31	31	31	31	31	31	186 (6)
Universal presentation	FAST	31	31	31	31	31	31	186 (6)
	M-SASQ	31	31	31	31	31	31	186 (6)

Number of patients per intervention		124	124	124	124	124	124	744
Number of practices per intervention		4	4	4	4	4	4	24

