The trial will incorporate cluster randomisation of practices to avoid the risk of contamination. Clinicians trained to deliver 'talk-based' advice or counselling become compromised in their ability to deliver alternative versions of such care; thus it is not practical for individual clinicians to deliver both control and intervention conditions in this trial. Therefore clinicians will consistently deliver a particular version of brief intervention. Cluster randomisation also provides an opportunity to pragmatically evaluate brief interventions in primary care in a way that will allow issues of implementation to be addressed from a practice perspective.

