### Study Hypotheses

• Targeted screening methods will result in greater implementation of screening activity than longer more broadly focused (universal) approaches.

• Motivationally-enhanced brief intervention for hazardous and harmful drinkers will be more effective than advice or written information, as follows: BLC > BA > PIL.

• Brief intervention (either advice or counselling) will be more cost effective than merely providing a patient information leaflet.

• Attitudinal, practical, skill, resource, and reinforcing factors will predict screening and brief intervention activity.

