### Sample size calculation

The sample size calculation was designed to account primarily for intervention level outcomes. Powering the study in this way will also account statistically for appropriate outcomes for screening approach and screening method. The primary outcome for this study is the proportion of patients who consume alcohol within recommended levels at 6 month follow up. A comprehensive meta-analysis [13] suggested that the difference between brief intervention and control is of the order 13%; that is a 5% reduction in the control group and 18% in the brief intervention group. Detecting a difference of this magnitude at the 5% significance level with 80% power, for a 2-sided test, requires 109 patients in each of the 3 groups and a total of 327. Our experience with other multi-centre randomized controlled trials of interventions for alcohol use disorders suggests that with assiduous follow-up the potential loss to follow-up across groups is of the order 25%. Taking this loss into accounts inflates the sample required to 145 in each group, a total of 435 patients.

The proposed study involves a cluster design and requires a statistical adjustment to account for any potential cluster effect. The literature, and our previous experience of trials in primary care [44], suggest an intra-class correlation coefficient of 0.04 is appropriate. Assuming a cluster size of 31 patients inflated the sample size calculation by a factor of 1.7 requiring 248 patients in each group and a total of 744, with an expectation that at least 558 will be followed up at 12 months.

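### The bootstrap behind the acceptability curves is justified by skewness alone; if it resamples patients as independent, the curves will be too certain, because practices are randomised

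*Protocol article*

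**What the plan says.** The Design section states that "The trial will incorporate cluster randomisation of practices to avoid the risk of contamination", and that practices are assigned to "1 of 3 intervention conditions (8 practices in each condition"). The Sample size calculation section draws the statistical consequence: "The proposed study involves a cluster design and requires a statistical adjustment to account for any potential cluster effect". It adds that the literature and earlier primary care trials "suggest an intra-class correlation coefficient of 0.04 is appropriate".

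One of the four study hypotheses is economic: "Brief intervention (either advice or counselling) will be more cost effective than merely providing a patient information leaflet".

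The Economic evaluation section gives the method for handling uncertainty: "Data will be bootstrapped to account for the expected skewness evident in economic cost data". Its announced output is the "construction of cost-effectiveness acceptability curves to illustrate the probability that the brief intervention is more cost-effective than usual care", at different monetary values of a QALY. The section mentions neither practices as clusters nor the unit to be resampled.

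The Planned analysis section brings in multi-level modelling only to look for interactions among screening approach, screening tool and intervention. It does not connect that modelling to costs or QALYs.

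**The concern.** Skewness and clustering are different problems. A bootstrap of individual patients deals with a skewed cost distribution, but it treats patients in the same practice as independent. The variation of incremental cost and incremental QALY between practices then drops out of the resampled distribution. With eight practices per arm, that component can be a large share of the total.

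The protocol's own text makes some clustering of costs plausible. Practice staff record the resources used, local values price the interventions, and staff, premises and training costs are included. Such items tend to be shared or similar within a practice.

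At stake is the curve that bears on the economic hypothesis. If its spread is too small, its values lie too far from 0.5, and brief intervention looks more surely cost-effective, or more surely not, than eight practices per arm can show. Correcting the regression for the drinking outcome would not help, because the economic analysis is not said to use it.

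**Working it through.** **Inputs from the protocol.** 8 practices per arm (Design). 31 patients recruited per practice, 25% loss and ICC 0.04 (Sample size calculation). Patients analysed per practice: 31 × 0.75 = 23.25.

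**Input not in the protocol.** An ICC for cost, QALY or net benefit. It is varied below from 0 to 0.10. The 0.04 is given for the sample size of the drinking outcome.

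**The plan's own inflation figure.** The protocol says: "Assuming a cluster size of 31 patients inflated the sample size calculation by a factor of 1.7 requiring 248 patients in each group". The path from 109 per group is 109/0.75 = 145.3, then 145 × 1.7 = 246.5, rounded up to 8 × 31 = 248. The factor 1.7 does not follow from its stated inputs: 1 + (31 − 1) × 0.04 = 2.20, or 1 + (23.25 − 1) × 0.04 = 1.89 for the patients followed up. That mismatch is a separate matter. The formula is used here, with a result for 1.7 alongside.

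**Formulas, if patients are resampled as independent.**
- Design effect: DE = 1 + (23.25 − 1) × ICC.
- True standard error divided by bootstrap standard error: √DE.
- A curve value p should read Φ(z(p)/√DE), taking incremental net benefit as approximately normal.

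Example at ICC 0.04: DE = 1.89, √DE = 1.375, and Φ(1.645/1.375) = Φ(1.197) = 0.884.

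| Assumed ICC | DE | √DE | 0.80 should read | 0.95 should read |
|---|---|---|---|---|
| 0 | 1.00 | 1.00 | 0.80 | 0.95 |
| 0.01 | 1.22 | 1.11 | 0.78 | 0.93 |
| 0.02 | 1.45 | 1.20 | 0.76 | 0.91 |
| 0.04 | 1.89 | 1.37 | 0.73 | 0.88 |
| 0.10 | 3.23 | 1.80 | 0.68 | 0.82 |

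With the plan's factor of 1.7 in place of DE, 0.95 becomes Φ(1.645/1.304) = 0.90.

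**Check by simulation.** 1,500 trials per ICC, 8 practices of 23 patients per arm, gamma-skewed net benefit, no true difference.
- ICC 0: true SD of the difference 0.1051, mean patient-level bootstrap SE 0.1035, ratio 1.02.
- ICC 0.04: 0.1435 against 0.1038, ratio 1.38 (formula 1.37).
- ICC 0.10: 0.1848 against 0.1028, ratio 1.80 (formula 1.80).

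The patient-level SE hardly changes as the ICC rises, so the bootstrap does not see the clustering.

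**Would resampling whole practices be enough?** At ICC 0.04 a practice-only bootstrap gave an SE of 0.1318 against 0.1435, about 8% too small (0.1318/0.1435 = 0.92). Most of this is the factor √((k − 1)/k) for k resampled units: √(7/8) = 0.94 with eight practices. Within arm-by-region strata of four practices it would be √(3/4) = 0.87. Hence the small-sample correction in the remedy, and the advice not to resample within those strata.

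**The case against.** The strongest reply is that the text contains no wrong analysis. The resampling unit is not stated, a practice-level or two-stage bootstrap is also a response to skewness, and a condensed article commonly leaves such detail to a fuller plan. The authors clearly know that the design is clustered. This stands as far as it goes. A reader might infer that the curves are too certain as a matter of fact, but the protocol does not support that, because it never says that patients will be resampled.

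The reply does not remove the point. The article did not leave the method open: it named the method and gave it one purpose. That purpose omits the adjustment which the sample size section calls required, and no other section supplies it for costs and QALYs.

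A reader might also turn the design effect of 1.89 into a false-positive rate, 2 × P(Z > 1.96/1.375) = 0.154 in place of 5%, or speak of cost-effectiveness intervals that are too narrow. The documents do not support that framing. The economic section names curves that illustrate a probability. It sets no threshold, proposes no test and announces no interval.

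Two further objections stand. The ICC of 0.04 is borrowed from the drinking outcome, and at ICC 0 nothing changes. Service use is to be valued at common national unit costs, which removes local price variation from that component. Finally, resampling patients does not in itself bias the incremental estimate; the point concerns its uncertainty.

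**Conclusion.** The point holds in conditional form. The economic section justifies its bootstrap by skewness alone and does not carry over the cluster adjustment, although only eight practices per arm are randomised. If patients are resampled as independent, the acceptability curves will be too certain.

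The size rests on three assumptions: patient-level resampling, 23.25 patients analysed per practice, and an ICC for net benefit that the protocol does not supply. The effect is nil at ICC 0, small at 0.01 and material at 0.04 and above, as tabulated. It does not touch the primary outcome. It does bear on a stated hypothesis, and it is cheap to settle before analysis.

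**What to change.** In the Economic evaluation section, state that uncertainty in cost and QALYs will respect the randomised unit, and that the acceptability curves will be built from that analysis. Either of two methods would serve:

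- a two-stage bootstrap that resamples practices within intervention arm and then patients within practice, keeps each patient's cost and QALY paired, and applies a small-sample shrinkage correction; or
- a bivariate multilevel model of cost and QALY with a practice random effect and a small-sample correction.

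Do not resample within arm-by-region strata, which hold only four practices each; handle region by adjustment. The simulation above did not cover the two-stage method with shrinkage or the bivariate model, so the chosen method should be checked at eight practices per arm before it is fixed.

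The change costs one sentence and slightly more programming, with no new data or patients. The downside is flatter curves.
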